## Methods

### Participants

Computer required sample size analysis for repeated measures ANOVA within-between interaction, with an effect size of 0.25 [medium effect size; average from effect sizes in changes by yoga in previous studies (9, 25)], a power of 0.80, an alpha error probability at 5%, for two groups (yoga and comparison) and two measurements (pre-and post-intervention) suggested a sample size of 34 for each sex.

We aim to collect complete data from at least 34 participants of both sexes (34 male and 34 female clients) to perform gender-specific analyses. Gender analyses will only be performed, if this number of participants can be reached.

Based on previous experience working with participants within correctional settings, we know that the attrition rate can reach 50%; therefore, our aim is to include approximately 120 participants.

Three institutions at the South West in Sweden have at this stage declared interest in participating in the study. Data collection is planned to take place for one and a half years' time, based on an estimated three months per institute (Figure 1). This three months period includes spreading advertisements and information about the study, collecting informed consents, six weeks of intervention (including pre- and post-intervention tests), and time for qualitative interviews to assess individual experiences of yoga classes. As the average time spent within SiS is calculated to be eight months, we will be able to perform intervention and data collection in each participating institute twice, six months apart during the planned data collection period (one and a half years) (Figure 1).

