### Procedure

Upon placement to the juvenile institution, the young people will be offered to participate in the study. Participation is voluntary, and SiS clients are ensured that participation in yoga or in a comparison group or non-participation should not affect the care they receive at SiS. All data is coded (pseudo-anonymized) and the code keys will be kept securely at each juvenile institution under the institution directors' responsibility, following SiS regulations. Upon completion of data assessment code keys will be destroyed. Only anonym data will be handled outside each SiS facility. With this procedure we assure that there is no possibility of identifying the individual from the collected information.

The study has a *quasi-experimental* design. Participants will receive a numeric code and will participate in the pre-intervention assessment, after which they will chose to participate in yoga classes (belonging to the “yoga group”) or not to participate in yoga classes (belonging to the “comparison group”) (Figure 2). The yoga group will participate in a 75 min yoga session, twice a week, for six weeks—as their leisure-time physical activity. During the same six-week period, the comparison group will participate twice a week (~1 h) in any, at the institution offered leisure-time physical activity (e.g., walking, gym training, and physical education class). Participants of the comparison group are asked to include ~10–15 min of relaxation at the end of their leisure-time physical activity.

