### Measures

Three different origins of data are included as measurements: (A) self-reported measures in the form of a survey, (B) heart rate measure, and (C) register data. A and B applied both at pre-intervention (Test 1) and post-intervention (Test 2), while the data from SiS's register will be combined with data only for those participants who complete all parts of the study.

The pre-intervention survey includes a question on yoga expectations, and the post-intervention assessment includes a question on time spent on yoga and the experience of yoga.

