#### C. Register Data

Register data concerning the participants' medications during the intervention, their school attendance and participation in physical activity classes during the study will be assessed based on registers kept by SiS.

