### Data Analysis

If the required number of male and female participants (at least 34 of each gender) is reached, then we will analyze the data separately by gender. Otherwise, the data will be pooled, and no gender-specific results will be presented.

All statistical analyses will be conducted using a significance level of *p* <0.05. Only complete post-attrition data will be analyzed. The comparison of the attrition rates between the two groups (“yoga” group and “comparison” group) will be calculated using Fisher's exact test. The Test 1 and 2 scores within the groups will be compared using the Wilcoxon signed-rank test. Mean changes and standard deviations will be calculated to identify differences within the groups. Mann–Whitney *U-*tests will be used for the continuous variables and Fisher's exact test for the categorical variables to compare differences between them. The effect sizes (Cohen's *d*) will be calculated to identify differences between the groups; an effect size of 0.2 will be considered a small effect, 0.5 a medium effect, and 0.8 a large effect. As data will be collected from three institutions, generalized estimating equations (GEE), that adjusts standard regression estimators for clustering, will be applied. The primary outcome is the level of psychological distress (BSI). Secondary outcomes' (craving, pain, affect, and aggressive antisocial behaviors) mediating and moderating effect will be also explored by conditional process analyses. We plan to conduct a mid-point analysis (about nine months after that data collection has started) to allow for better modeling of change trajectories.

To describe the adolescents' experiences of participating in yoga practice, with the help of a semi-structured interview guide (Supplementary Material), individual interviews will be performed. The adolescents will be contacted within 2 weeks after completing the yoga intervention. Content analysis will be used as a method for analyzing the interviews (52). The qualitative content analysis is performed stepwise identifying meaning units, condensing the meaning units, labeling meaning units with codes and thereafter identifying subcategories, categories ant themes. Content analysis makes it possible to describe the adolescents' experiences on both manifest and latent levels.

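### Every effect analysis is restricted to completers although up to half may leave, register data are not linked for leavers, and the one attrition check cannot show whether this biases the group contrast

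*Protocol article*

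**What the plan says.** The protocol article fixes the following:

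- **Analysis set (Data Analysis):** "Only complete post-attrition data will be analyzed".
- **Expected loss (Participants):** "the attrition rate can reach 50%; therefore, our aim is to include approximately 120 participants".
- **Register linkage (Measures):** "the data from SiS's register will be combined with data only for those participants who complete all parts of the study". Under Register Data the content is given as "Register data concerning the participants' medications during the intervention, their school attendance and participation in physical activity classes during the study".
- **Order of events (Procedure):** participants "will participate in the pre-intervention assessment, after which they will chose to participate in yoga classes" or the comparison activity. A Test 1 record therefore exists for anyone who leaves after that assessment. According to Measures, the pre-intervention survey also asks about expectations of yoga.
- **Attrition check (Data Analysis):** "The comparison of the attrition rates between the two groups" by Fisher's exact test.
- **Code keys (Procedure):** they are held at the institutions and destroyed once data assessment is complete.

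The primary outcome is distress on the BSI, self-reported at Tests 1 and 2. The group comparisons named are Mann-Whitney and Fisher tests, with GEE for clustering by institution. No covariates, imputation, weighting, comparison of completers with leavers, or sensitivity analysis for missing Test 2 scores is stated. Because the article itself sets the analysis set and the linkage rule, these are not details left to a fuller document.

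**The concern.** Participants choose their group, so the two groups may differ from the start. Restricting the analysis to completers adds a second selection step that need not work the same way in both groups. The article gives reasons to think that leaving is related to the outcome. Its Discussion says that high distress often hampers response to treatment, and distress is the primary outcome. It also reports that experts predicted 80–90% attrition if clients could not choose freely, so willingness to stay is expected to depend on attitude to the activity.

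The planned check compares how many leave, not who leaves. Two groups can lose equal shares of quite different adolescents. Meanwhile the leavers' Test 1 scores go unanalysed and their register records are never linked. Once the code keys are destroyed, that linkage cannot be made.

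At stake is whether the yoga contrast describes the participants who entered each group or only those who stayed. The Discussion proposes to use a positive result as the basis for national investment.

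**Working it through.** **Numbers at the stated ceiling.** With 120 enrolled and 50% attrition, 120 × (1 − 0.5) = 60 remain, so up to 60 participants with a Test 1 fall out of every effect analysis. The 50% is an upper figure, not a forecast.

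**Is this mainly a loss of power?** No. The plan's 34 per sex reproduces from the noncentral F for the within-between interaction, with f = 0.25, two measurements, α = 0.05 and an assumed pre-post correlation ρ = 0.5 (the article gives none):

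- λ = f² × N × m / (1 − ρ) = 0.0625 × 34 × 2 / 0.5 = 8.5, df 1 and 32, power 0.807.
- At the 60 pooled completers, λ = 0.0625 × 60 × 2 / 0.5 = 15, df 1 and 58, power 0.968.

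On that assumption pooled power is adequate, before any allowance for clustering. The issue is who remains.

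**When the completer contrast is biased.** For each group let p be the attrition share and g the mean change among leavers minus that among completers, in SD of change. Then:

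- full-group mean change = completer mean + p × g;
- full-group contrast − completer contrast = p_Y × g_Y − p_C × g_C (Y for yoga, C for comparison).

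The contrast is unbiased if the two products are equal. With p = 0.5 in both groups the shift is 0.5 × (g_Y − g_C). The article gives no value for g, so these differences are assumptions:

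| Difference in gap, g_Y − g_C | Shift of contrast |
|---|---|
| ±0.2 SD | ±0.10 SD |
| ±0.5 SD | ±0.25 SD |
| ±0.8 SD | ±0.40 SD |
| 0 | 0 |

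For scale, the plan calls d = 0.5 a medium effect, and 0.25 is half of that.

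**A second illustration.** Take a normal selection model with retained share r and an assumed correlation c between staying and improvement, acting in one group only. The completer mean shifts by c × φ(z)/r. At r = 0.5 this is c × 0.399/0.5:

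| c | Shift (SD of change) | Two-sided 5% rejection rate with no true effect, 30 completers per group |
|---|---|---|
| 0.1 | 0.08 | about 6% |
| 0.2 | 0.16 | about 9% |
| 0.3 | 0.24 | about 15% |
| 0.5 | 0.40 | about 33% |

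The even split of 60 completers is an assumption. If the same selection acts in both groups with 40% and 60% retained, the shifts fall to 0.03, 0.06, 0.10 and 0.16 SD. If it acts equally with equal retention, they cancel.

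**What Fisher's test can see.** By exact enumeration with 60 per group (assumed), its power is 0.54 for attrition of 40% versus 60%, and 0.16 for 45% versus 55%. In the first table attrition is equal in the two groups, so the test has nothing to detect even when the shift is 0.40 SD.

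**The case against.** Several points on the other side stand.

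- **Completer analyses are not always biased.** Equal weighted gaps cancel, as shown above, and a completer regression is valid if leaving depends only on covariates in the model. This limits the claim but does not remove it, because the tests named use no covariates and none is stated for the GEE.
- **Direction.** A reader might infer that dropout must favour yoga, because those who find it unhelpful leave. The article does not link attrition to disliking yoga; it cites only experience in correctional settings. Leavers could equally include adolescents who improved: the Discussion suggests that benefit may shorten care. The sign is therefore open.
- **Stopping classes.** A reader might also infer that someone who stops attending is refused Test 2. No section says so. Classes are voluntary throughout, and the post-intervention survey asks how much time was spent on yoga, so varying exposure is foreseen. The fault is ambiguity: neither complete data nor completion of all parts is defined. Because heart rate variability is recorded at the first and last sessions, the linkage rule could exclude someone who took Test 2 but missed the last session.
- **What the registers can do.** They hold no BSI or other survey outcome, so they cannot by themselves correct the result. They are auxiliary variables for a missing-at-random model, and the leavers' Test 1 scores matter at least as much. Nothing says those scores are destroyed.
- **Consent.** Linking records of detained adolescents who left raises a real consent question, and the restriction may have that basis. Consent wording can settle this; it does not justify excluding leavers who agree to linkage.
- **Attrition was considered.** Enrolment was raised and the design chosen to limit dropout. Both concern the number retained, not its selectivity.

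**Conclusion.** The point holds in this form: the plan bases every effect analysis on completers while allowing for up to half the sample to leave, and its only analysis of attrition cannot show whether the resulting contrast is biased. Bias arises if the dropout-completer gap, weighted by attrition share, differs between the groups and is not explained by modelled covariates. At the 50% ceiling, illustrative differences of 0.2 to 0.8 SD give shifts of 0.10 to 0.40 SD in either direction. These are not estimates: the gaps, the equal attrition and the group split are all assumptions.

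The documents do not support saying that the plan necessarily favours yoga or that register data would repair the result. It should be changed before consent is taken, because the linkage cannot be recovered once the keys are gone.

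**What to change.** 1. Replace the completers-only rule with a main analysis of all consenting participants who have a Test 1, by the group they chose. Use multiple imputation or inverse-probability weighting based on the Test 1 scales, yoga expectation, sex, institution and register variables.
2. State that Test 2 does not depend on class attendance, and define complete data and completion of all parts.
3. Link register data for everyone who consents and has not withdrawn permission, before the code keys are destroyed.
4. Compare completers with leavers at baseline within each group, alongside the Fisher comparison of rates.
5. Add a delta-adjusted sensitivity analysis with shifts in both directions and different shifts by group.
6. Keep the completer analysis as secondary.

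**Cost and limits.** The cost is modest analysis work and consent wording that covers linkage for non-completers. The main analysis would be valid under missing at random only. It removes neither bias that depends on unobserved post-test distress, which the delta analysis can only bracket, nor confounding from self-selection into yoga, which the article acknowledges as a limitation.

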##### Juvenile Care Adjusted Measure of Aggression

It is a SiS environment adapted version of the Prison Adjusted Measure of Aggression (PAMA), which assesses the self-reported frequency of state aggression and antisocial behavior in subjects within correctional settings (37). The Juvenile Care Adjusted Measure of Aggression (JCAMA) scale consists of nine items. The items are distributed over three subscales: a five-item Aggression scale, a two-item Antisocial Behavior scale, and a two-item Self-directed Aggression scale.

The Aggression subscale measures overt aggression and includes items on temper tantrums, verbal and indirect aggression, non-specific fighting, and physical assault against people. The Antisocial Behavior subscale consists of items on disciplinary problems at school and conflicts caused by own antisocial behavior. The Self-directed Aggression subscale includes items on self-injurious behavior and suicide attempts.

All the items are rated on a six-point scale based on the total number of occurrences over the past month: no occurrences = 0, one event = 1, two or three events = 2, four to nine events = 3, 10 or more events = 4, more events than can be counted = 5. The JCAMA score is the sum of the ratings on all nine items (total score) or the specific items in a certain subscale (subscale score). The JCAMA total score can range from 0 to 45; the Aggression subscale scores from 0 to 25; the Antisocial behavior scores from 0 to 10; and the Self-directed Aggression scores from 0 to 10.

The original PAMA's validity has previously been shown to be acceptable, and its test-retest reliability has been measured as fair (37), while the JCAMA reliability has not yet been tested.

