Reduced recidivism and substance use are not only valuable from a socioeconomic perspective, but they are also necessary for the promotion of a safe society for all and, of course, represent a vital benefit for the individual. The study population comprises a highly relevant group from the perspective of basic societal needs. There are about 550,000 15–19-year-old Swedish citizens today. 0.2% of these adolescents are institutionalized in SiS care yearly (4). The care provided to this small fraction of adolescents represents a considerable annual cost for society (1.6 million SEK/person for medication and 2.1 million SEK/person for placement in SiS care). If this vulnerable group's care and rehabilitation are not successful, it will continue to represent a considerable burden on society at several levels: criminality, medical health problems, social support needs, pain, and suffering of the individual and others.

An active heroin addict costs society 2.1 million and an amphetamine addict about 1.5 million SEK/year from an economic perspective. These figures encompass the expenses for their active use (criminality, legal authorities, and financial aid), medical and social care, and costs for their family's support.

In the event the present study can provide evidence on the positive effects of yoga for the clients of SiS institutions, it will provide a basis and rationale for making a strategic investment at the national level.

The positive effects of yoga at the individual level are proposed from strong scientific evidence. Studies have proven in adult populations that yoga can strengthen the practitioner's self-acceptance, purposefulness, and sense of responsibility (26). These qualities promote a more peaceful and safer environment in institutional settings and offer higher effectiveness of other treatments and school education programs. Yoga can also provide a foundation for the development of a prosocial lifestyle upon release. In other words, there is evidence that yoga empowers the individual yoga practitioner and thus improves his or her mental health and prosocial lifestyle. These novel effects of yoga practice emphasize the importance of testing yoga as complementary care for young people with behavioral and mental health problems.

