The duration and the type of yoga in the present study have been adjusted to the population. We use a shorter intervention time but more frequent training (six weeks twice a week, implying 12 yoga sessions) to optimally adapt to the participating institutes' possibilities. Several studies have proven that 8–10 weeks (once a week, therefore, 8–10 sessions) yoga has positive effects on mental health, behaviors, and self-control of adults in correctional setting (9, 25–27, 53). As our study population includes adolescent, it is essential to recognize that the brain goes through pruning (anatomically improving its efficiency) during this developmental period [see e.g., (54)]. During this time, the brain is increasingly susceptible to environmental effects; therefore, we speculate that eventual changes in adolescents' mental health and behaviors will be recognizable already after six weeks (12 sessions) of training. There are results indicating that short-term intensive interventions (four weeks, three times a week yoga classes) have a positive effect on adults' anxiety, depression, and stress (55). Importantly we use a specifically developed yoga (trauma-informed yoga), adapted to the most common psychiatric disorders (ADHD, PTSD, anxiety, and depression) in the adolescent study population.

The proposed study fills a gap in knowledge focusing on young people population in institutional care. If the study's hypothesis is confirmed, our results will verify and strengthen earlier findings in Sweden (9, 25, 26) regarding the benefits of yoga for a marginalized population, thus indicating the usefulness and value of yoga within juvenile institutional care at a national level.

One limitation of the proposed study is the fact that we won't be able to randomly distribute participants between groups, with other words, we could not rationalize a randomized controlled trial (RCT) design. A quasi-experimental design was chosen in agreement with the clinical and institutional experts, who predicted an unacceptable high attrition rate (80–90%) in case of not giving the possibility to the young clients to freely choose their participation in yoga classes.

Future RCTs should confirm our findings and prospective longitudinal studies need to investigate if yoga within SiS can potentially offer a prosocial activity upon release from institutions for young people.

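### Groups are self-chosen after the pre-test, but the named between-group tests cannot adjust, so a baseline difference can mimic or mask a yoga effect

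*Protocol article*

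**What the plan says.** The Procedure section has participants complete the pre-intervention assessment, "after which they will chose to participate in yoga classes" or decline them and join the comparison group. The Discussion concedes as a limitation that the investigators will not "be able to randomly distribute participants between groups".

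The Data Analysis section of the protocol article then sets out:

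- **Between groups:** Mann-Whitney U "tests will be used for the continuous variables", and Fisher's exact test for categorical ones, with Cohen's d as effect size.
- **Within groups:** Test 1 and Test 2 "scores within the groups will be compared using the Wilcoxon signed-rank test".
- **GEE:** to be applied because three institutions supply data. Its described role is to correct for clustering. No covariate is named.
- **Conditional process analyses:** for mediation and moderation by the secondary outcomes, not for confounding.
- **Primary outcome:** psychological distress on the BSI, in completers only.

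The Measures section adds a variable recorded before the choice is made: "The pre-intervention survey includes a question on yoga expectations". The analysis gives it no role. The Discussion says of a positive result that "it will provide a basis and rationale for making a strategic investment at the national level".

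**The concern.** When participants pick their own group after a baseline test, the groups can differ at the start in distress, motivation and belief in yoga. Each of these can also affect the later BSI score. A rank test of yoga against comparison attributes the whole difference to yoga. The document names tests that cannot adjust and gives its one regression model for the group comparison another purpose. So this is an analysis choice stated in the text, not just a detail left out.

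Within-group tests next to the group comparison add a second risk. A significant change in yoga and a non-significant one in the comparison group is easily read as an effect, although the two p-values do not compare the groups. At stake is the primary conclusion, on which a national investment argument may be built.

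**Working it through.** **1. The plan's own figure.** Participants section: effect size 0.25 (read as Cohen's f), power 0.80, alpha 5%, two groups, two measurements, 34 per sex. The pre-post correlation ρ is not stated; 0.5 is assumed. For the within-between interaction, λ = f²·N·m/(1−ρ) = 0.0625 × 34 × 2 / 0.5 = 8.5 with 1 and 32 degrees of freedom, which gives power 0.807. The 34 reproduces, as a total over both groups (ρ = 0.3 would give 46, ρ = 0.7 would give 22). So the arithmetic is not at issue. The interaction it powers is not among the tests named in the Data Analysis section.

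**2. Completers.** About 120 included at 50% attrition leaves 120 × 0.5 = 60, or 30 per group if the split is even (assumed).

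**3. Expected bias with no yoga effect.** Let yoga choosers start δ SD higher on BSI. The article gives neither δ nor ρ.

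- *Transient gap* (both groups regress to one common mean): the Test 2 difference is ρδ, the difference in change is −(1−ρ)δ, and the baseline-adjusted difference is ρδ − ρδ = 0.
- *Stable gap* (the groups differ lastingly): the Test 2 difference is δ, the difference in change is 0, and the baseline-adjusted difference is δ − ρδ = (1−ρ)δ.

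**4. False-positive rates.** Simulation, two-sided 5%, 30 per group, ρ = 0.5, 4,000 runs; the adjusted model is a regression of Test 2 on group and Test 1:

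| Gap δ | (1−ρ)δ | Transient: Mann-Whitney on change | Transient: adjusted | Stable: Mann-Whitney on change | Stable: adjusted |
|---|---|---|---|---|---|
| 0.2 SD | 0.10 SD | 6.4% | about 5% | 4.7% | 7.1% |
| 0.3 SD | 0.15 SD | 8.5% | about 5% | 5.6% | 10.5% |
| 0.5 SD | 0.25 SD | 14.5% | about 5% | 5.0% | 17.5% |

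With no gap, Mann-Whitney on change rejects in about 4%, so the test itself is sound.

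**5. Mann-Whitney on Test 2 scores.** With a transient gap of 0.5 SD the bias is 0.5 × 0.5 = 0.25 SD and about 15% of trials reject. With a stable gap the full 0.5 SD remains. Neither case is protected.

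**6. Direction.** If the more distressed choose yoga and the gap is transient, the change score favours yoga and the Test 2 score goes against it. If the less distressed choose yoga, both signs reverse.

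**7. Within-group tests.** Suppose both groups improve by the same 0.3 SD (assumed), with ρ = 0.5 and 30 per group. With no baseline gap, Wilcoxon is significant in 34% of trials for yoga and 32% for comparison, and in yoga alone in 23%. With a transient 0.5 SD gap these become 59%, 15% and 51%.

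**The case against.** **GEE is a regression and can carry covariates.** A covariate list is often left to a fuller document, so a reader should not infer that no adjustment will ever be made. That stands. But the article states a purpose for GEE, and it is clustering. The tests it names for the group contrast have no place for covariates. As written, the plan does not deal with selection.

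**Baseline adjustment is not proven to be right.** This stands in full. The adjusted model holds 5% only if the baseline gap is transient; if it is stable, the change score is the unbiased one. The documents do not settle which applies.

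**The Wilcoxon point imputes an inference.** The article nowhere says that significance in yoga alone will count as an effect, and with balanced groups the opposite pattern is equally likely. What stands is a request on reporting, not a charge of error.

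**The limitation is acknowledged.** The Discussion explains the lack of randomisation by predicted attrition of 80 to 90% and calls for later RCTs. There is an active comparison group, and the investment statement is conditional. This is fair, but no analytic remedy is tied to the limitation.

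**Three further inferences are tempting and not supported.**

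- That sex is ignored: separate analyses are planned if 34 of each sex are reached, so only the pooled fallback lacks it.
- That medication at Test 1 can be adjusted for: the Register Data section records medication during the intervention, and no pre-intervention variable is documented.
- That aggression recall biases the comparison. For that scale "All the items are rated on a six-point scale based on the total number of occurrences over the past month", so for new arrivals Test 1 may reach back before placement. That affects both groups, concerns a secondary outcome, and is not cured by the covariates proposed here.

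**Conclusion.** The concern holds in this form: groups are self-chosen, the named between-group tests cannot adjust, and no other named analysis is assigned to confounding. A baseline difference can therefore produce or mask an apparent yoga effect.

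Under the stated assumptions (no yoga effect, 30 per group, ρ = 0.5, gap 0.2 to 0.5 SD), the false-positive rate of Mann-Whitney on change is about 6 to 15% if the gap is transient and about 5% if it is stable. For the baseline-adjusted model it is about 5% and about 7 to 18% respectively. Mann-Whitney on Test 2 scores is biased either way. Gap, correlation and even split are assumptions, because the article gives none of them.

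A reader might conclude that selection and regression to the mean *will* be reported as a yoga effect. The documents do not support that: with no gap the error rate stays near 5%, and the direction depends on who chooses yoga.

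**What to change.** 1. Make the planned GEE the primary between-group analysis: Test 2 BSI on group, with Test 1 BSI, baseline yoga expectation, institution and round as covariates, and sex when the data are pooled.
2. Report a change-score model with the same covariates, without Test 1 BSI, as a sensitivity analysis. State that the two rest on different assumptions about the baseline gap, and discuss any disagreement.
3. Where Mann-Whitney is kept, say whether it is applied to change or to Test 2 scores.
4. Do not adjust for variables recorded during the intervention, such as register medication or attendance.
5. Present within-group changes descriptively with confidence intervals. Do not use the Wilcoxon tests as evidence of a yoga effect.
6. Word conclusions as adjusted associations.

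**Cost:** no new data collection and slightly more analysis. With three institutions and two rounds, and expectation entered as one score, the covariates use 2 + 1 + 1 + 1 + 1 = 6 degrees of freedom out of about 60 completers in a pooled analysis. In a sex-specific analysis they use 5 out of 34. Motivation that is not measured stays uncontrolled whichever model is used.
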